### 5.3 Determining sample size

We referred to the flare rate of the placebo arm in ‘Met Lupus’ trial and the flare rate from the BLISS-52, BLISS-76 and BLISS-North East Asia phase III trials. We supposed the flare rate to be 10% in MMF group and 30% in Control group. Z test with unpooled variance (alpha=0.0568, beta=0.1964, power=0.8036) was used for sample size calculation. A sample size of 58 patients per group would provide the trial with 80% power at a two-sided alpha error of 0.05 to detect a difference between the two groups using the software PASS version 11.0. Taking an estimated 10% drop-out into account, a sample size of 65 patients per group could fulfill the statistical requirement. The sample size was calculated using PASS version 11.0 software as follows:

Two Independent Proportions (Null Case) Power Analysis  
Numeric Results of Tests Based on the Difference: P1 - P2  
H0: P1-P2=0. H1: P1-P2=D1<>0. Test Statistic: Z test with unpooled variance

|       | Sample
Size
Grp 1
N1 | Sample
Size
Grp 2
N2 | Prop H1
Grp 1 or
Trtmnt
P1 | Prop
Grp 2 or
Control
P2 | Diff
if H0
D0 | Diff
if H1
D1 | Target
Alpha | Actual
Alpha | Beta   |
|-------|-------------------------------|-------------------------------|-------------------------------------|-----------------------------------|---------------------|---------------------|-----------------|-----------------|--------|
| Power | 58                            | 58                            | 0.1000                              | 0.3000                            | 0.0000              | -0.2000             | 0.0500          | 0.0568          | 0.1964 |

Reference:

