## **6. Sample size calculation**

We referred to the flare rate of the placebo arm in 'Met Lupus' trial and the flare rate from the BLISS-52, BLISS-76 and BLISS-North East Asia phase III trials. We supposed the flare rate to be 10% in MMF group and 30% in Control group. Z test with unpooled variance ( $\alpha=0.0568$ ,  $\beta=0.1964$ ,  $\text{power}=0.8036$ ) was used for

sample size calculation. A sample size of 58 patients per group would provide the trial with 80% power at a two-sided alpha error of 0.05 to detect a difference between the two groups using the software PASS version 11.0. Taking an estimated 10% drop-out into account, a sample size of 65 patients per group could fulfill the statistical requirement. The sample size was calculated using PASS version 11.0 software as follows:

| Two Independent Proportions (Null Case) Power Analysis                      |                         |                         |                                     |                                   |                     |                     |                 |                 |        |
|-----------------------------------------------------------------------------|-------------------------|-------------------------|-------------------------------------|-----------------------------------|---------------------|---------------------|-----------------|-----------------|--------|
| Numeric Results of Tests Based on the Difference: P1 - P2                   |                         |                         |                                     |                                   |                     |                     |                 |                 |        |
| H0: P1-P2=0. H1: P1-P2=D1<>0. Test Statistic: Z test with unpooled variance |                         |                         |                                     |                                   |                     |                     |                 |                 |        |
|                                                                             | Sample
Size
Grp 1 | Sample
Size
Grp 2 | Prop H1
Grp 1 or
Trtmnt
P1 | Prop
Grp 2 or
Control
P2 | Diff
if H0
D0 | Diff
if H1
D1 | Target
Alpha | Actual
Alpha | Beta   |

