### **8.2 Analysis principles**

- 1) For the primary outcome assessed at two levels (mild-to-moderate and severe flares), Bonferroni correction was used and two-sided at a significance level of 0.025. Other tests were performed two-sided at the significance level of 0.05. The confidence level for all confidence intervals (CI) will be 95%.
- 2) The number of observations used in the analysis will be reported.
- 3) The statistical analysis plan is drafted prior to database lock, and it includes a detailed description of the statistical analyses. The statistical analyses were performed using SPSS Statistics (version 23.0), GraphPad Prism (version 8.0), and R software

(version 4.0.0). Figures will be plotted using GraphPad Prism (version 8.0) and R software (version 4.0.0).

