### **8.5 Primary outcome**

Flare proportion was defined as categorical variables, data were expressed in the form of frequency (percentages). The primary outcome was the proportion of patients with flares (including mild-to-moderate flares and severe flares) during follow-up. Safety of Estrogens in Lupus Erythematosus National Assessment-Systemic Lupus Erythematosus Disease Activity Index (SELENA-SLEDAI) Flare Index (SFI) was used for assessing disease flares in this trial. Pearson Chi-square or Fisher's exact tests were used to compare between-group differences. We first calculated the total flare rate, and then calculated mild-to-moderate flare rate and severe flare rate, respectively.

For the primary outcome, Bonferroni correction was used and two-sided at a significance level of 0.025. A more stringent statistical criterion was used. Relative risk (RR) was employed to compare the proportion of patients with the end point between MMF group and Control group. Severe flare-free survival proportion was estimated by using the Kaplan-Meier method in the intention to MMF group and Control group with a log rank test. Regarding patients who dropped out of the study, we collected all of the data during follow-up period. For patient who loss to follow-up, we did not collect the data for the subsequent time after lost to follow-up event. We used the ITT set for primary outcome calculation. All of the patients were included in the denominator. We estimated the severe flare-free survival proportion of the MMF group and Control group in both ITT and PP Set using the Kaplan-Meier method.

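### Holm's step-down procedure would test the two flare levels with more power than plain Bonferroni at the same 5% familywise bound: a cheap improvement, not an error

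*Combined protocol and SAP*

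**What the plan says.** SAP 8.2 defines the family and the rule. It opens with "For the primary outcome assessed at two levels (mild-to-moderate and severe flares" and continues that "Bonferroni correction was used and two-sided at a significance level of 0.025". Protocol 10.2 gives the same rule, and SAP 8.5 repeats the 0.025 level with the comment "A more stringent statistical criterion was used". None of the three sections has a step-down, hierarchical or alpha-recycling rule.

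Three other statements bear on the point.

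- SAP 8.5 also says "We first calculated the total flare rate, and then calculated mild-to-moderate flare rate and severe flare rate, respectively". It does not say whether the total flare rate is a confirmatory test. The primary-outcome rows of SAP Table 3 list only the severe and the mild-to-moderate proportions.
- On intervals, SAP 8.2 says "The confidence level for all confidence intervals (CI) will be 95" per cent.
- The sample size (SAP 6, protocol 5.3) rests on one overall pair of rates: "We supposed the flare rate to be 10% in MMF group and 30% in Control group". It states that "A sample size of 58 patients per group would provide the trial with 80% power at a two-sided alpha error of 0.05". No rates by flare level are given.

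**The concern.** Under plain Bonferroni each flare level is held at 0.025 whatever the other level shows. Suppose severe flares give P = 0.01 and mild-to-moderate flares give P = 0.04. The plan must call the second level negative, although control of the familywise error at 5% does not require it. Holm would declare both.

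The usual practical reason to stay with Bonferroni is that it comes with simple matching simultaneous intervals, here 97.5% for each level. This SAP reports 95% intervals, so it does not use that advantage. At stake is some power on the second flare level, in a trial where power per level is low.

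**Working it through.** **Inputs.** From the documents: overall flare 30% (Control) versus 10% (MMF); 58 per group, raised to 65 for 10% drop-out; two-sided 0.025 per level; Pearson chi-square or Fisher's exact test. SAP 8.5 keeps all patients in the denominator, so 65 per arm is used for the main figures. Assumed: how the 30% and 10% divide between the levels, and that each patient counts at one level only.

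**Step 1: the plan's own figure.** Exact binomial enumeration of the two-sided unpooled Z test with 58 per arm, 10% versus 30%, target alpha 0.05, gives power 0.8036 and actual alpha 0.0568. Both match the plan. The normal approximation agrees: n = (1.960 + 0.842)² × (0.10×0.90 + 0.30×0.70) / 0.20² = 58.9. For drop-out, 58 / 0.90 = 64.4, so 65.

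**Step 2: Holm has the same error bound.** This takes each single test to hold its nominal level.

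- Both levels null: any rejection needs the smaller P to be at or below 0.025. Its probability is at most 0.025 + 0.025 = 0.05 under any dependence.
- One level null: a false rejection needs that level's P to be at or below 0.05, so the probability is at most 0.05.

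Holm rejects whatever Bonferroni rejects. It adds the second level when one P is at or below 0.025 and the other lies above 0.025 and up to 0.05.

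**Step 3: size of the gain.** Simulation, 400,000 trials per scenario, 65 per arm, Pearson tests. Entries are Bonferroni → Holm.

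| Severe / mild-to-moderate, Control vs MMF (assumed) | Severe | Mild-to-moderate | Both | At least one |
|---|---|---|---|---|
| 15/15% vs 5/5% | 0.363 → 0.410 | 0.362 → 0.408 | 0.114 → 0.208 | 0.611 → 0.611 |
| 10/20% vs 3/7% | 0.242 → 0.299 | 0.477 → 0.506 | 0.102 → 0.188 | 0.616 → 0.616 |
| 20/10% vs 7/3% | 0.478 → 0.506 | 0.240 → 0.298 | 0.101 → 0.187 | 0.617 → 0.617 |

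The gain per level runs from 0.506 − 0.478 = 0.028 to 0.298 − 0.240 = 0.058, or about 3 to 6 points. A further split (severe 12% vs 3%, mild-to-moderate 18% vs 7%; 200,000 trials) moves the chance of both from 11.9% to 21.3%. Among trials with at least one significant level, Holm adds the second in (0.208 − 0.114) / 0.611 = 15% of cases in the first row and 14% in the other two.

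With 58 evaluable per arm, the gain per level for the three tabled splits is about 2.5 to 5 points, and the chance of both moves from about 0.08 to 0.15-0.16. With 65 per arm and both levels null, the simulated familywise error is 0.047 under either rule.

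**Step 4: sensitivity to the test.** If Fisher's exact test replaces Pearson when an expected count is below 5 (an assumption; the SAP gives no switching rule), the 12/18% vs 3/7% split uses Fisher for severe flares in 48% of trials. The chance of both then moves from 9.1% to 18.0%.

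**Step 5: what Holm does not change.** The first rejection still needs P at or below 0.025. At that level the planned 30% versus 10% contrast has exact power 0.710 (58 per arm) or 0.762 (65 per arm) with the unpooled Z test, and 0.699 or 0.754 with chi-square.

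**Step 6: a third test.** If the total flare rate is also tested at 0.025, the Bonferroni bound is 3 × 0.025 = 0.075. The simulated familywise error is about 0.06. Holm over the two levels alone would not cure that.

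**The case against.** The plan's rule is valid, prespecified and consistent across three sections, and SAP 8.5 presents the stricter level as deliberate. That stands, so this is a matter of efficiency.

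Holm leaves the chance of winning on at least one level unchanged, and nothing in the plan requires both levels to be significant. That also stands. The benefit is limited to the second level, and the chance of both stays low under either rule.

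Every rate by level is assumed. The simulations also count each patient at one level only, whereas SAP 4 has patients with mild-to-moderate flares followed to week 96 with all episodes recorded, so a patient could count at both. These points limit the precision of the figures. They do not affect the ordering of the two rules, which holds for any rates and any dependence.

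Holm has a cost: its matching simultaneous intervals are less simple. A reader might infer that Bonferroni gives power away for nothing, and that is too strong. The cost is small here because the SAP's 95% intervals do not match Bonferroni either.

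A larger gain is tempting to cite. If the tested pair were any flare (30% vs 10%) and severe flare (15% vs 4%, assumed), power for severe flare would rise from 46% to 57%. But SAP 8.2 names mild-to-moderate and severe flares as the two levels, so this pair does not represent the plan.

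**Conclusion.** This is an optional improvement at very low cost. Plain Bonferroni at 0.025 controls the familywise error for the two levels named in SAP 8.2 and protocol 10.2. Holm keeps the same bound and never rejects less. Under the assumed splits, with 65 per arm and Pearson tests, it adds about 3 to 6 points per level and moves the chance of both from about 10-12% to about 19-21%. The levels are lower where Fisher's test applies.

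A reader might infer more, in two ways. One is that the plan contains a multiplicity error in its two-level correction; the documents do not support that, because 0.025 + 0.025 = 0.05. The other is that Holm would make a positive primary result more likely, or make good the sizing at 0.05. It does neither, since the first rejection stays at 0.025.

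The statement about the error rate assumes exactly two confirmatory tests. The total flare rate in SAP 8.5 leaves that open, and the family must be settled whichever correction is kept.

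**What to change.** Make the change before unblinded results are seen. In SAP 8.2, SAP 8.5 and protocol 10.2, replace the Bonferroni sentence by:

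*The comparisons of the proportion with mild-to-moderate flare and the proportion with severe flare are tested by the Holm procedure at familywise two-sided 0.05: the smaller P value is compared with 0.025 and, if significant, the larger with 0.05.*

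Report Holm-adjusted P values in SAP Table 3. For two tests these are twice the smaller P (capped at 1) and, for the other, the larger of that value and its own P.

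State in SAP 8.5 that the total flare rate is outside this family and descriptive. If it is meant as a third confirmatory test, apply Holm to all three: smallest P at 0.05/3 = 0.0167, next at 0.025, largest at 0.05.

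The cost is one sentence in three places and a line on the total flare rate, with no added patients or visits. Matching simultaneous intervals become less simple, so the SAP should say that its 95% intervals are not adjusted for multiplicity. The mismatch between sizing at 0.05 and testing at 0.025 needs its own correction.

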### **8.3 Data quality control**

All responsible data collectors will be trained at the beginning of this study (GCP training). Double entry is required for all variables and double validation is required for all other variables. The hospital coordinator at each collaborating site ensures that all data needed are collected.

### **8.4 Patients characteristics and baseline comparisons**

Description and statistical inference of the following baseline characteristics will be presented for Control group and MMF group.

In the descriptive statistics, data were expressed as frequencies (percentages) for categorical variables and medians (interquartile) or means  $\pm$  standard deviations (SD) for continuous variables. Additionally, t-tests were used to compare between-group differences in continuous variables after exploring the normality of data distribution using the Shapiro-Wilk test. Mann-Whitney U tests were used to compare continuous variables with skewed distributions. Pearson Chi-square or Fisher's exact tests were used to compare between-group differences in categorical variables. Relative risk (RR) was used to compare the proportion of patients with the endpoint between the MMF and Control groups. We estimated the severe flare-free survival proportion of the MMF group and Control group using the Kaplan-Meier method with a log rank test. Hazard ratios (HR) were calculated by Cox proportional-hazards model.

### **8.5 Primary outcome**

Flare proportion was defined as categorical variables, data were expressed in the form of frequency (percentages). The primary outcome was the proportion of patients with flares (including mild-to-moderate flares and severe flares) during follow-up. Safety of Estrogens in Lupus Erythematosus National Assessment-Systemic Lupus Erythematosus Disease Activity Index (SELENA-SLEDAI) Flare Index (SFI) was used for assessing disease flares in this trial. Pearson Chi-square or Fisher's exact tests were used to compare between-group differences. We first calculated the total flare rate, and then calculated mild-to-moderate flare rate and severe flare rate, respectively.

For the primary outcome, Bonferroni correction was used and two-sided at a significance level of 0.025. A more stringent statistical criterion was used. Relative risk (RR) was employed to compare the proportion of patients with the end point between MMF group and Control group. Severe flare-free survival proportion was estimated by using the Kaplan-Meier method in the intention to MMF group and Control group with a log rank test. Regarding patients who dropped out of the study, we collected all of the data during follow-up period. For patient who loss to follow-up, we did not collect the data for the subsequent time after lost to follow-up event. We used the ITT set for primary outcome calculation. All of the patients were included in the denominator. We estimated the severe flare-free survival proportion of the MMF group and Control group in both ITT and PP Set using the Kaplan-Meier method.

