## **6.5 Methods of subject assignment**

Participants were randomly assigned (1:1) using blocks of four to receive either MMF (MMF group) or a control treatment (Control group). A statistician from the Clinical Trial Center of Ruijin Hospital, [name], who was masked to trial allocation generated the randomization sequences by a computer algorithm. Then, random numbers were written on the cards and packed in sequentially numbered envelopes that were opened when the patients were enrolled. [name] assigned patients to different groups according to the number on the card. Only Assessors were masked to the group allocation. Eligible subjects were recruited from the Department of Rheumatology and Immunology of Ruijin Hospital and the Department of Rheumatology and Immunology of the other two clinical centers.

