### 12. Study content schedule

| content \ time                | Screening period | Follow-up period |         |         |         |
|-------------------------------|------------------|------------------|---------|---------|---------|
|                               | Screening day    | Week 24          | Week 48 | Week 72 | Week 96 |
| Informed consent form         | √                |                  |         |         |         |
| Inclusion/Exclusion Criterias | √                |                  |         |         |         |
| Physical examination          | √                | √                | √       | √       | √       |
| SLEDAI-2000 Index             | √                | √                | √       | √       | √       |
| Blood routine examination     | √                | √                | √       | √       | √       |
| Urine routine examination     | √                | √                | √       | √       | √       |

|                     |   |   |   |   |   |
|---------------------|---|---|---|---|---|
| ALT&AST             | ✓ | ✓ | ✓ | ✓ | ✓ |
| Scr                 | ✓ | ✓ | ✓ | ✓ | ✓ |
| ESR & CRP           | ✓ | ✓ | ✓ | ✓ | ✓ |
| Complement 3 & 4    | ✓ | ✓ | ✓ | ✓ | ✓ |
| Anti-dsDNA antibody | ✓ | ✓ | ✓ | ✓ | ✓ |
| immunoglobulin G    | ✓ | ✓ | ✓ | ✓ | ✓ |
| SF-36 score         | ✓ | ✓ | ✓ | ✓ | ✓ |
| Medication          | ✓ | ✓ | ✓ | ✓ | ✓ |
| Adverse events      | ✓ | ✓ | ✓ | ✓ | ✓ |

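### The primary flare comparison makes no use of baseline SLEDAI-2000: the unadjusted test is valid, but a cheap and probably small gain in precision is missed

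*Combined protocol and SAP*

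**What the plan says.** SAP 8.5 (Primary outcome) gives the test: "Pearson Chi-square or Fisher's exact tests were used to compare between-group differences". It gives the effect measure as: "Relative risk (RR) was employed to compare the proportion of patients with the end point between MMF group and Control group". The analysis is on the ITT set at a two-sided level of 0.025. SAP 8.2 explains that this level is a Bonferroni correction for the two flare levels, mild-to-moderate and severe.

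No covariate, stratified test or adjusted sensitivity analysis for the primary outcome appears in either document. The Cox model in SAP 8.4 lists no covariates, and protocol 10.5 (Subgroup analysis) is blank.

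The study content schedule in SAP 12 has a row for the "SLEDAI-2000 Index" at screening and at each follow-up visit. The SAP's mock Table 1 reports the baseline score by arm.

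Randomisation is 1:1 in blocks of four with no stratification factor stated (protocol 6.5, SAP 8.1). Patients are "recruited from the Department of Rheumatology and Immunology of Ruijin Hospital and the Department of Rheumatology and Immunology of the other two clinical centers".

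**The concern.** Disease activity at entry can vary. Rash, arthritis, alopecia, oral ulcers and mild blood-count changes are all allowed, and allocation does not balance on activity. A change of 3 or more in SELENA-SLEDAI is one of the flare criteria in SAP 3.1, so a link between the baseline score and flare is plausible. If the link exists, leaving the score out gives a wider interval than the collected data allow. A chance imbalance between the arms would then show in Table 1 with no planned way to account for it. Adjusting only after seeing such an imbalance would look data-driven, so any adjustment has to be fixed in advance.

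Precision matters here because the trial was sized at alpha 0.05 while the primary outcome is tested at 0.025.

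**Working it through.** **Inputs from the documents.** Rates, protocol 5.3: "We supposed the flare rate to be 10% in MMF group and 30% in Control group". Sizing test: "Z test with unpooled variance (alpha=0.0568, beta=0.1964, power=0.8036) was used for sample size calculation". Enrolment: "Taking an estimated 10% drop-out into account, a sample size of 65 patients per group could fulfill the statistical requirement". Analysis level: two-sided 0.025 (SAP 8.5).

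**Input not in the documents.** The prognostic strength of baseline SLEDAI-2000. I assume a standardised covariate with an odds ratio (OR) for flare of 1 to 3 per SD and hold the marginal rates at 30% and 10%.

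**Step 1. Reproduce the plan's own figure.** Summing exact binomial probabilities over all outcomes of the two-sided unpooled Z test, with 58 per arm and 10% versus 30%, gives power 0.8036. With both arms at 30% the actual alpha is 0.0568. Both match the plan. For drop-out, 58 / 0.90 = 64.4, rounded up to 65.

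**Step 2. The planned test at the planned level.** With 65 per arm and alpha 0.025, exact power is 75.4% for Pearson and 68.6% for Fisher. The exact size with both arms at 30% is 0.0256 for Pearson and 0.0160 for Fisher. In simulation at nominal 0.05, leaving out a prognostic covariate gave a Pearson type I error of 0.052 to 0.053. The unadjusted test is therefore valid.

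**Step 3. Effect of adjustment.** The model is flare = a + b × arm + c × baseline score, where b is the risk difference, with HC2 variance and a t reference. The logistic score test is a separate check. Entries are at alpha 0.025 with 65 per arm.

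| Assumed OR per SD | Linear model, HC2, t: change in power (points) | Separate run, 12,000 trials, t reference | Logistic score test, 20,000 trials: unadjusted → adjusted |
|---|---|---|---|
| 1.0 | −0.4 | – | 75.9% → 75.6% |
| 1.5 | +0.5 | +0.7 | 75.5% → 76.5% |
| 2.0 | +2.7 | +2.5 | 75.7% → 78.6% |
| 2.5 | +4.2 | +3.9 | – |
| 3.0 | +6.0 | – | 75.3% → 82.2% |

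Type I error of the linear model was 2.3% to 2.6%. The variance of the risk difference was about 1% higher at OR 1, and about 2%, 5% and 12% lower at OR 1.5, 2 and 3.

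The t reference matters. With no covariate at all, an HC2 test with a normal reference has exact power 76.2% against 75.4% for Pearson. That 0.8 points comes from the variance formula and not from adjustment.

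**Step 4. Chance imbalance.** The SD of the between-arm difference in mean baseline score is √(2/65) = 0.175 covariate SDs, so a 2-SD imbalance is 0.35. At OR 3 the flare risk rises by about 0.14 per covariate SD, which shifts the observed difference by 0.35 × 0.14 = 0.049. That is about 5 points against the planned 20. At OR 1.5 the shift is about 2 points.

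Across all trials this averages out. Among null trials with an imbalance above 0.35 (about 4.6% of trials), the unadjusted test at nominal 2.5% rejected in 5.4%, 7.5% and 10.0% at OR 2, 2.5 and 3. A model with the score and a non-prognostic centre term rejected in 3.0%, 1.9% and 3.3%. At OR 1.5 both rejected in 2.8%. Each figure rests on about 460 trials (4.6% of 10,000), so the direction is more reliable than the exact values.

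**Step 5. Centre.** A Mantel-Haenszel test by centre at alpha 0.025 moves power from about 75.3% to 74.0% with no centre effect and to about 74.8% with a moderate one. With a strong one (control rates of about 15% to 55%) it rises to about 77%. The change is about −1 to +2 points. Centre sizes are not given and were assumed.

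**Step 6. Events.** Expected flares are 65 × 0.30 + 65 × 0.10 = 19.5 + 6.5 = 26. Arm and score leave 26 / 2 = 13 events per term. Adding two centre terms leaves 26 / 4 = 6.5.

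**The case against.** The case for leaving the plan alone is good. The sample size assumes an unadjusted two-proportion test, and the analysis is of the same kind. No stratification factor is stated, so the analysis omits no design factor. The test holds its size, and a chance imbalance under randomisation is neither bias nor average type I error inflation. All of this stands, and it is why the point is an improvement only.

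The gain also rests on an assumed prognostic strength. No section says that baseline SLEDAI-2000 predicts flare. The serological signal that SAP 2 links to flares is rising anti-dsDNA. Excluding major organ involvement probably narrows the spread of the score, which favours the lower end of the range. This stands too, and the no-association case is therefore included above.

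A further objection is that an adjusted odds ratio would answer a different question from the planned relative risk. It does not apply to a standardised risk ratio, which keeps the planned scale. A last objection is that 0.025 is set for the two flare levels, and the SAP's mock Table 3 lists those two as primary, so adjusting only the any-flare comparison would be incomplete. That is correct, and the fix covers it.

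A reader might infer that the unadjusted test is biased, that precision is certainly being lost, or that ignoring centre is a flaw. The documents support none of these readings.

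**Conclusion.** The point holds as a cheap improvement. The planned analysis is valid but uses no baseline information, although SLEDAI-2000 is scheduled for every patient before treatment. At 65 per arm, 30% versus 10% and alpha 0.025, adjustment adds about 0.5 to 6 power points to a base of about 75% if the OR per SD lies between 1.5 and 3. It costs about 0.4 points if the score is not prognostic. The gain depends wholly on that assumed range.

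The benefit in a trial with a visible baseline imbalance is conditional on that imbalance, and it is clear only at OR 2 and above. The gap between the sizing alpha of 0.05 and the testing level of 0.025 is a separate and larger matter, and adjustment does not reliably repair it.

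**What to change.** In SAP 8.5, prespecify as the primary estimate the marginal risk ratio and risk difference for any flare, adjusted for baseline SLEDAI-2000 as a continuous covariate. Standardise the two arm risks over all analysed patients. Name the variance estimator and reference distribution, for example HC2 with a t reference, and say how the interval for the risk ratio is formed. The simulations above cover the risk difference, so the risk-ratio interval deserves a short simulation check before database lock.

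Apply the same model to the severe and mild-to-moderate levels tested at 0.025 where event counts allow, and state the minimum count and the fallback. Leave centre out of the primary model. Keep the Pearson or Fisher result as the supportive unadjusted analysis.

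The cost is SAP wording and a few lines of R, which the SAP already lists, with no new data. The downside is a power loss of under one point if SLEDAI-2000 turns out not to be prognostic.
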